**Fig. 1 Fig1:**
[figure not shown]
Study design, remote setting and procedures of the trial, and online data management of the trial

### Participants

A total of 122 participants aged 50 and older will be enrolled according to the following inclusion criteria:
Have access to a tablet (i.e., iPad or Android) or a computer with an Internet connection,Absence of significant cognitive impairment (i.e., score of 19/23 or higher on the telephone version of Mini-Mental State Examination, MMSE) [29],Absence of non-cardiopulmonary limitation to exercise (e.g., arthritis) or of a severe exercise intolerance,Absence of respiratory disease (e.g., severe asthma, COPD, severe COVID-19 related symptoms) as documented with a medical questionnaire,Absence of cardiovascular disease (e.g., chronic heart failure, somatic aortic stenosis, atrial fibrillation, malignant arrhythmias, any documented atherosclerosis disease) as documented with a medical questionnaire.

No systematic dropout criteria are fixed as dose-response relationships will be explored.

### Remote setting and procedures, online data management

There is no on-site visit planned in the course of the study. The research team has implemented online tools that allow performing all assessments, exercise monitoring, and cognitive training entirely remotely. The research project will be advertised to active members of physical exercise centers and to community-dwelling adults through online study announcements (e.g., videos, interviews, newsletters). Potential participants will be able to express their interest by leaving a voice mail or sending an email to an email address dedicated to the study. The name and contact information of potential participants will be compiled in a password-protected encrypted file located in a cloud folder with restricted access. The anonymization table is built at this stage, where each contact is associated with an anonymous study I.D. number. A two-stage screening process will be used to select participants (timepoint T-1; Table 1). Initial contact will be made over the phone by a member of the research team. During this pre-screening call, only potential participants with no major physical or medical limitations to exercise and with access to the Internet and necessary technology will be selected. They will then receive the information and consent form by email, and the preliminary call will be scheduled with a member of the research team. During the preliminary call, the information and consent form will be presented to the potential participants, and they will be given the opportunity to provide oral consent. They will then be required to send written consent by email. If oral consent is obtained, the cognitive (MMSE) and physical (PARQ+) screenings will then be performed with a research assistant and will later be reviewed by a neuropsychologist and a kinesiologist, respectively. Once the research team receives the written consent by email and ensures eligibility, the participant will be considered enrolled. A technology tutorial will then be scheduled to ensure that Internet access and tools are ready and sufficiently mastered by participants. Collection of measurements and training data all along the study will be managed by assessors and trainers using online case report forms specifically dedicated to each testing session. Participants will receive automatic standardized communications by email to transmit study information like appointment schedules, links to self-reported questionnaires, and training guidelines. A non-overwriting process will ensure data integrity: all form submissions will be recorded in a journal fashion. Moreover, all data entries will be traceable and associated with a timestamp along with the identity of the research team member who completed the data entry. To ensure the blinding of the study, data collection will be divided into two sections on the online platform: training and evaluations. Research team members will receive different access based on their roles. The above-described procedure is summarized in Fig. 1.

**Table 1 Tab1:** List of assessments across the study timepoints according to the remote method used

Remote method	Domain	Procedure	T-1	T0	T1	T2	T3
**Phone call**	**-**	Written informed consent	X				
		Mini-Mental State Examination	X				
		Physical activity readiness questionnaire	X				
		Technology tutorial	X				
**Online videoconference**	**Cognition**	Montreal Cognitive Assessment		X	X	X	X
		Oral Trail Making Test		X	X	X	X
		Verbal Fluency Test		X	X	X	X
		Digit Span test		X	X	X	X
		Similarity Test		X	X	X	X
		Rey auditory verbal learning test		X	X	X	X
		Computerized trained cognitive task		X	X	X	X
		Computerized transfer cognitive task		X	X	X	X
	**Physical functions**	One leg balance test		X	X	X	X
		5-time Sit-to-stand test		X	X	X	X
		Timed Up and Go test		X	X	X	X
		4-meter walking speed test		X	X	X	X
**Online self-reported forms**		Matthews Questionnaire		X	X	X	X
	**Quality of life**	12-Item Short Form Survey		X	X	X	X
	**Mood and anxiety**	State Anxiety Inventory		X	X	X	X
		Geriatric Depression Scale		X	X	X	X
		Perceived Stress Scale		X	X	X	X
		Perseverative Thinking Questionnaire		X	X	X	X
		Connor-Davidson Resilience Scale 10		X	X	X	X
		Intolerance of Uncertainty Scale		X			
		Trait Anxiety Inventory		X			
		Anxiety sensitivity Index		X			
	**Social environment**	Social and Community Involvement Questionnaire		X	X	X	X
		Lubben Social Network Scale		X	X	X	X
	**Sleep**	Pittsburgh Sleep Quality Index		X	X	X	X
		Berlin Questionnaire		X	X	X	X
	**Nutrition**	Short Diet Questionnaire		X			X
	**Prior Physical activity**	Physical Activity Scale for the Elderly		X			
	**Cognitive reserve**	Cognitive reserve Questionnaire		X			
	**Gender**	Bem Sex-Role Inventory		X			
	**Medical history**	Medical Questionnaire		X			
	**COVID-19 repercussions**	QCOVID Questionnaire		X			

### Interventions

After being randomly (see the “Randomization and blinding” section) assigned to one of the 2 study arms, participants will receive a group-specific training guide. The training guide contains recommendations about the nature, intensity, and frequency of the training sessions. Participants will then attend an introductory session over the phone given by their training coach. Participants will be invited to follow the training guide while adjusting their dose as they see fit.

#### Physical exercise

Participants will be encouraged to complete a home-based physical exercise using video capsules available via Facebook or Youtube, created by the Centre ÉPIC of the Montreal Heart Institute’s team of kinesiologists. The videos last approximately 15 min and include a 3- to 5-min warm-up, followed by a 10-min training, and finally by a 2-min cool-down period (https://tinyurl.com/epic-icm). The exercises do not require any equipment and comprise aerobic, muscular strengthening, flexibility, and/or balance exercises. For each exercise, several difficulty levels are described to allow participants to perform the exercise according to their physical capacities. Participants will be invited to perform exercise sessions at least 5 times per week and could be encouraged to do more during the weekly monitoring. This recommendation aims to provide a target for a minimal amount of physical exercise [30] that all participants can introduce and autonomously maintain in their routine regardless of the sanitary context, their initial physical condition, or prior exercise routine. The exercise sessions can be performed at home using the video capsules, as well as other video or web-based training programs. As sanitary measures and confinement regulations could change during the course of the study, participants could also engage in outdoor activities (e.g., walking or cycling). For each exercise session, participants have to report its duration, intensity, and the nature of the activity via a follow-up agenda that will be provided by their training coach. Participants will assess the intensity of their exercise using the modified Borg Rating of Perceived Exertion (RPE) graduated from 0 to 10, where 0 indicates low and 10 high intensity.

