##### Dose-Response exploration

The type of activity, its frequency, duration, and intensity (i.e., according to the Borg scale) will be considered to compute the dose of physical exercise. The weekly dose of physical exercise will be converted in kcal and in METs using the Compendium of Physical Activities (i.e., coding scheme classifying specific physical activities by their rate of energy expenditure) [68, 69]. The effect of physical exercise dose on cognitive and physical functions will be evaluated according to participants’ mean weekly dose during the 6 months of intervention. Based on the overall study sample distribution, participants will be classified into three groups: higher, medium, and lower doses of physical exercise (i.e., tercile split). How the dose of physical exercise affects the primary and the secondary outcomes will be addressed by a repeated measures ANCOVA model, adjusted for age, sex, and education, including the effects of the intervention (physical exercise alone or combined with cognitive training), time (pre at baseline, mid at 3 months, post-intervention at 6 months) and dose groups (lower, medium or higher doses). An exploration of the dose-response effect for cognitive training will also be performed within the combined physical exercise and cognitive training intervention group. The dose of cognitive training will be considered according to its mean weekly duration. How the dose of cognitive training affects the primary and the secondary outcomes will be addressed by a repeated measures ANCOVA model, adjusted for age, sex, education, and the dose of physical exercise, including the effects of time (pre at baseline, mid at 3 months, post-intervention at 6 months) and dose groups (lower or higher doses of cognitive training; median split).

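### Self-rated Borg exertion feeds an energy-expenditure dose, and the exploratory dose-response model leaves out baseline fitness

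*Protocol article*

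**What the plan says.** **What is recorded.** In the protocol article, Interventions, Physical exercise: "For each exercise session, participants have to report its duration, intensity, and the nature of the activity via a follow-up agenda". The intensity item is a perceived-exertion rating: "Participants will assess the intensity of their exercise using the modified Borg Rating of Perceived Exertion (RPE) graduated from 0 to 10". No other session-level measure of intensity is described. The same section says of the exercises that "several difficulty levels are described to allow participants to perform the exercise according to their physical capacities".

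**How the dose is built.** Data analysis, Dose-Response exploration, lists activity type, frequency and duration, and adds that "intensity (i.e., according to the Borg scale) will be considered to compute the dose of physical exercise". It continues: "The weekly dose of physical exercise will be converted in kcal and in METs using the Compendium of Physical Activities". The Compendium is described there as a "coding scheme classifying specific physical activities by their rate of energy expenditure".

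**How the dose is used.** The mean weekly value over the six months is cut into terciles. These enter a repeated measures ANCOVA "adjusted for age, sex, and education, including the effects of the intervention", time and dose group. Baseline fitness is not among the covariates, although Table 1 schedules the Matthews questionnaire at T0 and the secondary-outcome section uses it to predict VO2max. Under Planned data analysis, the exercise dose is also a covariate in the main ANCOVA.

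**The concern.** A perceived-exertion rating says how hard a session felt to that person. Energy expenditure is an absolute quantity. If the rating raises the MET or kcal value given to a session, two people who do the same activity for the same time receive different doses, and the less fit one receives more.

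The dose-response comparison is not randomised. Participants choose their own amount of exercise, and fitness may affect both that choice and the change in outcome. A dose that itself depends on fitness adds a second route for confounding, and adjustment for age, sex and education closes neither route fully.

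This matters for a stated aim, since the Background sets out to explore which amount of home exercise gives the most benefit. The limitations section also offers the dose-response analysis as a partial answer to the lack of a control group.

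**Working it through.** The plan gives no figure for this point, so there is nothing to reproduce. The check follows the rating through the dose and then illustrates direction and size. All numerical settings below are assumptions, because the article gives neither the rating-to-MET rule nor any distribution of fitness.

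**1. Same activity, same minutes.** Assume relative load = (MET − 1)/(capacity − 1) and rating = 10 × relative load. For an activity truly costing 4 METs:
- capacity 6: 10 × 3/5 = 6.0
- capacity 8: 10 × 3/7 = 4.3
- capacity 10: 10 × 3/9 = 3.3

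The ratio of ratings between capacities 6 and 10 is (3/5)/(3/9) = 1.8. Let the assigned MET be proportional to rating^w. The less fit person's recorded dose is then 1.8^w times the fitter person's: 1.0 for w = 0, 1.34 for w = 0.5 and 1.8 for w = 1. The true ratio is 1.

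**2. Whole-sample simulation.** Settings: 122 people; capacity mean 8 METs, SD 1.5; log-SD of weekly volume 0.5; 300 runs per setting. True load is common to all, half scaled to capacity, or fully scaled. The correlation of volume with fitness is 0 or 0.3.

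| Load | Volume–fitness r | Recorded dose v fitness, w = 0 / 0.5 / 1 | True dose v fitness | In a different tercile from true dose, w = 0 / 0.5 / 1 |
|---|---|---|---|---|
| Common | 0 | −0.01 / −0.21 / −0.36 | about 0 | 17% / 17% / 27% |
| Common | 0.3 | 0.30 / 0.07 / −0.13 | 0.28 to 0.29 | 18% / 17% / 29% |
| Half scaled | 0 | 0.00 / −0.11 / −0.21 | 0.15 to 0.16 | 15% / 18% / 27% |
| Half scaled | 0.3 | 0.30 / 0.19 / 0.06 | 0.42 to 0.43 | 14% / 18% / 27% |
| Fully scaled | 0 | 0 / 0 / 0 | 0.30 | 22% / 20% / 24% |
| Fully scaled | 0.3 | 0.29 / 0.29 / 0.28 | 0.53 to 0.54 | 20% / 19% / 23% |

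Three things follow.
- Whenever the rating has weight (w = 0.5 or 1), recorded dose is tilted towards the less fit compared with true dose.
- The sign of its own correlation with fitness is not fixed. It is negative in some rows, nil in one and positive in others. In the first row the top tercile is 0.44 to 0.77 SD less fit than the bottom for w = 0.5 to 1.
- Removing the rating is no cure. With fully scaled load the gap from true dose is the same at w = 0, because a dose blind to intensity misses the fitter people's harder work. Much of the tercile misplacement is also present at w = 0.

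**3. What a remedy gains or loses.** A further simulation, also under assumed settings, let true intensity vary between people.
- With a common load and full weight on the rating, a dose from type and duration alone correlated 0.91 with true dose, against 0.84 for the rating-weighted dose.
- With self-scaled load the order reversed: 0.84 against 0.87 to 0.92.
- With a common load and a link between fitness and gain, adding baseline estimated fitness to the model brought false positives from 6–9% down to about 5%. It raised power from 21–44% to 40–58%.
- In the other settings the extra covariate cost almost nothing.

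**The case against.** The strongest reply is that the decisive step, how a rating changes a MET value, is not in the article. The Compendium classifies activities, so activity type anchors the rate, and the rating might only choose between levels of one activity. That rule may stand in the full protocol. Participants also pick a difficulty to suit their capacity, so identical exercise at different fitness is not the general case. All of this stands, and it is why no size can be given.

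Stronger readings are tempting, and the documents do not support them.
- A reader might infer that the dose groups rank people by low fitness. Step 2 shows this only in some scenarios; with self-scaled load, or when fitter people do more, the link vanishes or reverses.
- A reader might map ratings straight to 3, 5 or 8 METs and score the recommended 5 × 15 = 75 minutes as 225, 375 or 600 MET-min, a 2.7-fold range. That lets the rating alone set the rate, which the section does not say.
- A reader might simulate one true intensity for everyone and find large losses of power. The rating then carries no intensity information by construction. With rating = 5 − b × fitness + noise of SD 0.8 and b from 1.0 to 1.5, its correlation with fitness is −1/√1.64 = −0.78 to −1.5/√2.89 = −0.88, which nothing in the article supports.
- A reader might infer bias in the main intervention × time test, because the dose is a covariate there. Arms are randomised and receive the same exercise component, so a fitness-related error in dose gives no evident reason for it. Adjusting for a quantity measured after randomisation is a separate question.

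It is also fair that the analysis is labelled exploratory, that the Background defines dose as including intensity, and that the limitations section says tracking devices would measure exercise better.

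What survives is narrower: a fitness-dependent rating goes into an absolute dose, and the model comparing dose groups omits a fitness estimate that is already collected.

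**Conclusion.** The point holds in limited form. Given the same activity and minutes, any positive weight on the Borg rating credits the less fit with more relative to their true energy expenditure. This rests on perceived exertion being relative to capacity and on the rating raising the assigned MET value. The amount is unknown: in the assumed scenarios the recorded dose's correlation with fitness spans −0.36 to +0.30, and 14% to 29% of people fall in a different tercile from their true dose, part of it random noise that has nothing to do with the rating.

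As planned, the dose-group comparison is open to confounding by baseline fitness. The consequence is confined to an exploratory analysis, though one tied to a stated aim. It is a modest point, worth acting on because the remedy uses data in hand.

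**What to change.** In Dose-Response exploration:

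1. Add the T0 Matthews fitness estimate and its interaction with time as covariates in the dose-response models, except where the Matthews estimate is itself the outcome. The interaction is needed because the question concerns change; a main effect alone would adjust only the level.
2. Keep the Borg-weighted dose as the main definition, since dropping the rating loses real intensity information.
3. Report a sensitivity analysis in which the dose is computed from activity type, frequency and duration alone, with mean weekly rating as a separate term. Agreement between the two would show that conclusions do not hinge on the rating.

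The cost is one or two more covariates and a second exploratory analysis, with no new data collection. The gain is partial. The Matthews estimate is predicted from sex, age, anthropometry and self-reported activity, so it overlaps with covariates already in the model. The limitations section itself acknowledges error in such equations when used for change. It will reduce the confounding without removing it.

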#### Physical exercise and cognitive training

The combined multidomain intervention will include home-based physical exercise and cognitive training. Home-based physical exercise will be exactly similar to the conditions described in the previous section. Due to the important variations observed in the short-term effect of exercise on cognitive performances [31], home-based cognitive training will either take place prior to the exercise session or at least 3 h post-exercise training. Participants will be asked to complete their cognitive training in a quiet and comfortable setting without distraction. Both validated computerized cognitive tasks and video capsules will be provided to the participants. Participants will be encouraged to perform at least three sessions per week (30 min/session): two sessions of computerized cognitive tasks and the other one dedicated to the video capsules.

For the computerized cognitive training sessions, the following three tasks will be available: (1) dual-task training that requires participants to maintain and prepare for many response alternatives and to share attention between two concurrent tasks (i.e., Dual-task [32]), (2) inhibition training, which requires the participants to refrain from giving an automatic response (i.e., Stroop task [33]), and (3) working memory training, which asks participants to maintain and update information in working memory to recall items presented earlier (i.e., N-Back task [34]). Each cognitive task lasts approximately 15 min possesses its respective sets of visual stimuli (e.g., letters, numbers, symbols) and matching button symbols. Participants will be instructed to perform the tasks as fast as possible while maintaining accuracy. The three tasks will be presented in a fixed order for all the participants. The level of difficulty of each cognitive task will be gradually increased over the course of the participant’s cognitive training to avoid cognitive task automatization and to maintain stimulation [35]. These computerized tasks will also include visual feedback as well as a histogram of daily performances to encourage improvement and maintain motivation.

The remaining weekly session consists of a strategy-based training performed once a week via video capsules. This training is an adapted version of the MEMO+ program [36]. Participants will be instructed on different mnemotechnics (e.g., face-name association, visual imaging), as well as on age-related changes in memory. In addition, the strategy-based training also includes capsules aiming to help participants develop strategies to manage multiple aspects of their daily life such as sleep, anxiety, and nutrition. Participants will be asked to complete a follow-up agenda and mark days and times when they took part in the various cognitive training sessions to track their cognitive training adherence. Training adherence for computerized tasks will also be monitored online.

#### Remote monitoring and counseling

Once a week, training coaches will call participants over the phone to (1) motivate them to stay engaged in their training and to (2) collect exercise and cognitive training data reported by participants in their follow-up agenda during the previous week. The training coach will also provide and update information about training resources available online, track adherence, and advise participants according to their training characteristics and study training guidelines. Information about physical exercise and cognitive training sessions collected during these calls will allow to track the weekly dose of exercise and cognitive training and to adapt the recommendations given to the participant accordingly.

### Measures

Tests and self-reported questionnaires performed during the preliminary call and the four testing sessions are listed in Table 1. Information about demographics, chronic diseases, comorbidities, and chronic medications will be recorded using a medical questionnaire at baseline. A COVID-19 questionnaire (i.e., QCOVID) will address the social and financial consequences of the COVID-19 pandemic on participants, as well as its impact on their physical activity routines. The QCOVID will also document if the participant and his close circle were tested and/or affected by COVID-19 and ask if they previously developed COVID-19 symptoms, if applicable.

